#### Usual care group

The CG participants receive usual care regarding pain management by participating centres. The treating physicians assess pain and prescribe analgesics. However, if participants raise concerns to RAs about pain or side effects, they are encouraged to contact their physicians. No specific counselling is provided.

### Data collection

Both quantitative and qualitative data will be collected from March 2016 until December 2018. Patients in both groups complete a daily pain and symptom diary; patients and FCs fill in questionnaires. The same 6-week data collection protocol is applied via in-home visits at baseline and during weeks 1 and 6. In the IG, data are collected by the IN. In order to minimize diffusion of the intervention to CG participants, an RA collects data in the control group. Between in-home visits at baseline and weeks 1 and 6, patients/FCs receive brief telephone calls every second week, during which the RA ensures that the pain diary is being completed on a daily basis.

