**Methods:**

This mixed methods project combines a multi-centre randomized controlled clinical trial with qualitative data collection techniques and includes 210 patients recruited from three oncology outpatient clinics. FCs involved in patients’ pain self-management are also invited to participate. After baseline evaluation, eligible participants are randomized to a 6-week intervention group and a control group. Both groups complete a daily pain and symptom diary. Intervention group patients/FCs receive the weekly psychoeducational PRO-SELF© Plus PCP interventions; control group patients receive usual care. After completing the six-week study procedures, a subsample of 7–10 patients/FCs per group and hospital (*N* = 42–60) will be interviewed regarding their pain management experiences. Data collection will take place from April 2016 until December 2018. An intent-to-treat analysis and generalized linear mixed models will be applied. Qualitative data will be analysed by using interpretive description. Quantitative and qualitative results will be combined within a mixed method matrix.

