### Recruitment

Specifically trained nurses from the outpatient clinics work as research assistants (RAs) for the study. All RAs are experienced registered nurses or graduate students in nursing who have received study-specific training by the study coordinator (HR). RAs screen potential participants and verify inclusion criteria via patient files and discussions (regarding life expectancy, etc.) with their treating physicians. If the initial inclusion criteria are met, the RAs contact the patients directly during their outpatient appointment to check whether they have experienced repeated pain that they would rate on an NRS as ≥3 over the last week, are able to understand, read and write German, and have access to a telephone. The RAs then inform patients about the study and invite them to participate. Each patient is also asked if an FC is involved in their daily pain self-management. If yes, the FC is also invited to participate in the study. Written information and consent forms (including those for FCs, if necessary) are then given to the patient. After at least 24 h, an RA contacts each patient (or patient/FC dyad) again to provide verbal information to the FC as needed, ask about their decision regarding participation, and collect the signed written consent form. In all settings, these written informed consent forms are stored safely in the Investigator Site File (ISF) by the RAs. Only afterwards are participants randomized to the IG or CG. Patients and FCs have the right to withdraw from the study at any time without consequences.

Concerning the recruitment of participants for qualitative data collection, all patients (and FCs) are asked at the beginning of the main study whether they are willing to participate in an interview following completion of the study’s 6 weeks of procedures. At the end of the final home visit, the intervention nurse (IN) or an RA asks selected patients (and FCs) whether they are still willing to participate in the interview. They then provide verbal and written information and obtain written consent from those who agree. Purposive sampling is applied to ensure approximately equal sample sizes per study site, as well as variation regarding pain intensity, intervention adherence, age, gender, education, living situation, and tumour entity.

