Concerning the tailored intervention components, the IN reviews each pain diary with the associated patient/FC, assesses the appropriateness of the analgesic prescription and the side effect management, and teaches the patient/FC how to adjust the prescribed analgesics in response to changing pain conditions and side effects. Adherence to analgesic medication instructions and the IN’s recommendations is assessed and discussed with the patient/FC at each subsequent visit, after which modifications to the pain and side effect management plan are made as needed. The intervention is provided during in-home visits (baseline, weeks 1 and 6), followed by weekly in-home or telephone visits. The number, type (in-home visit or phone call) and frequency of visits are determined by defined criteria as follows: pain score > 3 on an NRS, patient is dissatisfied with pain management, patient adherence with pain medication or recommendations < 50%. If one or more of these criteria apply, the IN schedules an in-home visit; if none apply, she schedules a phone call. In addition, a reinforcement phone call is scheduled after major changes to the pain management plan.

For quality assurance and analysis, all intervention sessions and phone calls are audio recorded. The primary investigator and the study coordinator review audio recordings of visits and report their observations using an audit checklist based on the intervention protocol. In order to enhance the intervention’s implementation, they and the INs promptly discuss any deviations. They continue to monitor audiotapes until a 95% protocol adherence rate is achieved. Afterwards, audio-recordings are reviewed at random.

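### The intervention nurse collects the outcome forms in one arm and a research assistant in the other, and the arm-specific baseline visit conflicts with the abstract's order of baseline and randomization

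*Protocol article*

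**What the plan says.** In the Protocol article, Data collection, the collector depends on the arm: "In the IG, data are collected by the IN", and "In order to minimize diffusion of the intervention to CG participants, an RA collects data in the control group". The timetable is common to both arms: "The same 6-week data collection protocol is applied via in-home visits at baseline and during weeks 1 and 6". Patients complete the diary, and patients and family caregivers (FCs) fill in the questionnaires themselves.

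The Intervention group section places treatment at the same visits: "The intervention is provided during in-home visits (baseline, weeks 1 and 6), followed by weekly in-home or telephone visits". The same section has the nurse go through each diary with the patient or FC, and use the baseline PPQ to find knowledge gaps.

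Under Quantitative data, the primary outcomes are four side effects, self-efficacy and knowledge for patients, and self-efficacy and knowledge for FCs. The Blinding section rules out blinding because the nurses use the diary and the PPQ in the intervention.

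On the order of events, the abstract says "After baseline evaluation, eligible participants are randomized to a 6-week intervention group and a control group". The Recruitment section, after describing collection of signed consent, says "Only afterwards are participants randomized to the IG or CG".

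**The concern.** In an unblinded trial with self-reported outcomes, who receives the answers can affect the answers. At week 6 an IG participant hands ratings of confidence and knowledge to the nurse who has taught and coached them. A control participant hands the same forms to someone who has given no counselling. A wish to please, or to appear to have learned, can then act in one arm only. Because collector and arm coincide completely, no model can separate a collector effect at week 6 from a treatment effect.

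Baseline raises a second question. Aims 1 and 2 are analysed with group-by-time models and change scores, which lean on a baseline that is comparable by design. If baseline is taken once allocation is known, and in the IG at a visit that already belongs to the intervention, that comparability is no longer guaranteed.

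**Working it through.** **Collector and visit, side by side**

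| | IG | Control group | Source |
|---|---|---|---|
| Instruments and schedule | same | same | Data collection; Table 2 |
| Completion | by patient/FC | by patient/FC | Data collection |
| Collector | IN | RA | Data collection |
| Intervention delivered at baseline, week 1 and week 6 visits | yes | no | Intervention group; Usual care group |
| Nurse reviews diary with patient/FC | yes | no | Intervention group |

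In Table 2, PPQ/FPQ, self-efficacy and HADS are taken only at weeks 0 and 6, which are visits at which the IG collector is also delivering the intervention. The CAS is weekly and the diary is daily.

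**Do the stated reasons require this?**

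1. Limiting diffusion explains why INs stay away from control participants. It does not explain why an RA could not receive forms in the IG.
2. The nurse's use of the diary and PPQ requires the IN to see those data. The stated use of the PPQ is to assess baseline knowledge, so it does not require the IN to collect the week-6 PPQ. Self-efficacy is not named as an intervention input.

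**Order of baseline and randomization**

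1. Abstract: baseline evaluation, then randomization.
2. Recruitment and Random assignment: consent, then randomization. No baseline assessment is named in between, but none is excluded.
3. Data collection and Intervention group: the baseline home visit has an arm-specific collector and, in the IG, is an intervention visit. Both need a known allocation.

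Items 1 and 3 cannot both hold if they refer to the same baseline assessment.

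**Illustrative size**

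The plan's own figure first: 136 / (1 − 0.35) = 209.2, rounded up to 210, as stated. 136 evaluable patients means 68 per arm.

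The documents give no size for a reporting bias. Assume a shift of b standard deviations in the IG, no true effect and a two-sided 5% test of two means. The standard error in SD units is √(2/68) = 0.171, and

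P(reject) = 1 − Φ(1.96 − b/0.171) + Φ(−1.96 − b/0.171)

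| Assumed b | Normal approximation, 68 per arm | t-test, 68 per arm | Normal approximation, 105 per arm |
|---|---|---|---|
| 0 | 5.0% | 5.0% | 5.0% |
| 0.1 | 9.0% | 8.9% | 11.2% |
| 0.2 | 21.5% | 21.2% | 30.5% |
| 0.3 | 41.7% | 41.2% | 58.5% |

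The 105-per-arm column (210 / 2) shows that a larger sample does not dilute such a bias; it makes a false positive more likely.

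**The case against.** The case on the other side has several sound parts.

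- A reader might infer that outcomes are measured differently in the two arms. The protocol does not support that. Forms, timing and self-completion are the same, and nothing says that the nurse reads items aloud, scores them or watches completion. The difference is in who collects and in what setting.
- A reader might take it as stated that baseline follows allocation. No sentence says so, the flow chart is not shown, and the Recruitment sentence orders consent and randomization only. It is an inference, though a strong one, from the arm-specific baseline visit. It justifies asking for reconciliation, not asserting the order.
- A reader might go further and call the baseline contaminated and the damage beyond repair. That is too strong. The PPQ is used to find knowledge gaps, so it is presumably answered before tailored teaching. A collector shift that was equal at baseline and week 6 would cancel in change scores, and an affected baseline can be left out by comparing week-6 values directly. What cannot be removed by analysis is a shift present at week 6 only, or larger then. After six weeks of coaching, that is the pattern to worry about.
- Side effects are not gathered only at the week-6 visit. Nausea, emesis and concentration difficulties come from the daily diary, and the nurse's review of the diary is part of the intervention. The concern is therefore sharpest for self-efficacy and PPQ/FPQ.
- The rejection rates rest on an assumed shift. They also use a sample size derived from pain, which is secondary here, and a single t-test where mixed models are planned. FC numbers will differ.

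The absence of blinding is openly disclosed. That does not answer the point, because unblinded participants and nurses do not by themselves require a different collector in each arm.

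**Conclusion.** The concern holds in a limited form. The arm-dependent collector is explicit, is fully confounded with treatment and is avoidable at week 6 for the questionnaires. It leaves week-6 self-efficacy and PPQ/FPQ open to a reporting bias that the analysis cannot separate from the effect of the intervention. The order of baseline and randomization is inconsistent between the abstract and the Methods as they read together, and must be reconciled.

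The size of any bias is unknown. The figures of about 9%, 21% and 41% are conditional on assumed shifts of 0.1, 0.2 and 0.3 SD at 68 per arm. They show what such a shift would do and are not evidence that this trial has one.

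This should be changed because the remedy is cheap. It does not invalidate the design.

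**What to change.** 1. **Baseline.** After consent and before requesting allocation, the RA obtains the baseline questionnaires from patients and FCs, then passes a copy of the PPQ/FPQ to the IN for teaching. State the order of consent, baseline and randomization in the same way in the abstract, Recruitment, Data collection and Intervention group sections.
2. **Week 6.** In both arms, patients and FCs complete PPQ/FPQ, self-efficacy and HADS alone before the final visit. They hand them over sealed for the RA or data entry, unopened by the IN.
3. **CAS.** Leave it visible to the IN. The CAS section ties the score to a constipation management plan, so any change to who sees it must be reconciled with that section.
4. **Diary.** Acknowledge as a limitation that the diary side-effect items remain exposed, because the IN reviews the diary as part of the intervention.

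Cost: a short amendment, envelopes and some extra RA time at consent, when the FC must also be available. RAs already collect signed consent before randomization. There is a small risk of late or missing week-6 forms, which should be watched because the plan already expects 35% attrition. If data collection is too far advanced to change, report the arm-dependent collector as a limitation and state the order of baseline and randomization actually followed.

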### Quantitative data: variables and measurement

Table 2 provides an overview of the study variables and data collection points for patients and FCs.

**Table 2 Tab2:** Study variables and measurement timetable

Study variable	Instrument	Assessed in patients	Assessed in FCs	Week 0	Week 1	Week 2–5	Week 6
Demographics, patient	Patient Information Questionnaire	X		X			
Demographics, FC	FC Information Questionnaire		X	X			
Clinical data	Medical Record Review Form	X		X			
Average pain and worst pain	Pain management diary^a:^ Brief Pain Inventory (BPI)	X		X	X	X	X
Pain alleviation through pain medication		X		X	X	X	X
Pain interference with function		X		X	X	X	X
Duration of pain Bowel movements and use of laxatives Side-effects of pain and cancer treatment	Pain management diary^a:^	X		X	X	X	X
Knowledge of cancer pain	Patient Pain Questionnaire	X		X			X
	Family Pain Questionnaire		X	X			X
Constipation	Constipation Assessment Scale	X		X	X	X	X
Self-efficacy	Self-Efficacy Questionnaire in patients with cancer	X		X			X
	Caregiver version of the Self-Efficacy Questionnaire		X	X			X
Anxiety and depression	Hospital Anxiety and Depression Scale	X		X			X
Functional status	Eastern Cooperative Oncology Group Performance Status	X		X			X

Note. ^a^Pain management diary: daily assessment of average and worst pain, pain alleviation, and pain interference with function via *BPI* Brief pain inventory as well as duration of pain, bowel movements/ use of laxatives, side effects of pain and of cancer treatment via pain management diary

Questionnaires employed in this study are applied in their German versions, for which validity and reliability have been established. The primary patient outcomes are selected analgesics’ side effects (constipation, nausea, emesis, and concentration difficulties), self-efficacy, and knowledge of cancer pain management. Primary FC outcomes are self-efficacy and knowledge of cancer pain management. The secondary outcomes are patients’ average and worst-pain intensity. Anxiety, depression, functional status, and cancer-related symptoms are measured as covariates. Our analytical models will also control for age, education, time since diagnosis and current disease status.

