#### Pain management diary

A pain management diary is used to assess analgesics’ side effects for each 7-day period. Patients are asked to rate 12 side effect items on an 11-point NRS (0–10: 0 = no symptom experience; 10 = strongest imaginable symptom experience). Our analysis will focus on constipation, nausea, emesis, and concentration difficulties. On a second 11-point NRS (0 = no pain; 10 = strongest imaginable pain) patients also rate their daily average and worst pain intensity.

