#### Constipation assessment scale (CAS)

The CAS, an 8-item self-report tool, is completed weekly to measure the presence and severity of constipation (0 = no problem, 1 = some problem, 2 = severe problem). The total possible score ranges from 0 (no constipation) to 16 (severe constipation). A score of ≥2 will trigger the use of a constipation management plan. This scale’s validity and reliability have been established [46, 47].

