### Data analysis

Quantitative data will be compiled and analysed using SPSS 24.0. Data will be retrieved from the SecuTrial® database. Data will be systematically examined for out of range values and data inconsistencies. As appropriate, descriptive statistics will be calculated, including means and standard deviations for interval variables and frequencies, as well as percentages for categorical variables. An intent-to-treat analysis will be applied, using a significance level of .05 [55]. Although premature withdrawal is expected to be a random process, participants who completed the study will be compared with those who did not based on demographics, treatment group and other salient variables.

#### Data analysis for aim 1

Generalized linear mixed models will be applied to determine differences between the IG and the CG analgesic side effect developments throughout the intervention. This approach allows calculation of the main group and time effects, and of group-by-time interaction. The influence of missing data on the model results will be examined using sensitivity analysis [56]. Change scores for each patient as well as Cohen’s d will be calculated for each variable of interest.

#### Data analysis for aim 2

Our quantitative analysis will use descriptive statistics to summarize PPQ/FPQ items’ distribution characteristics. Generalized linear mixed models will be applied to determine differences between the IG’s and the CG’s knowledge of cancer pain management throughout the intervention. The influence of missing data on the model results will be examined using sensitivity analysis [46]. Change scores for each patient/FC as well as Cohen’s d will be calculated for each variable of interest.

For qualitative data analysis, transcript data will be stored and analysed in ATLAS.ti 7. Field notes and audiotapes of telephone calls, home visits and interviews will serve as qualitative data to explore both the IG’s and the CG’s the learning processes concerning knowledge of cancer pain and pain self-management. Data will be analysed via interpretive description–an approach using stepwise, systematic and iterative processing of data to arrive at a meaningful description and interpretation [57].

Information from quantitative and qualitative data collection will be combined within a mixed method matrix. Qualitative and quantitative results related to each German PPQ/FPQ item will be integrated in a final synthesis [39, 58].

#### Data analysis for aim 3

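### Eight primary outcomes stand unranked at a single .05 level, and constipation has two instruments with neither named as primary; for the side-effect aim alone the family-wise error is about 16–19% if any one significant result is read as efficacy

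*Protocol article*

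**What the plan says.** The section on quantitative variables and measurement sets the outcome hierarchy. For patients: "The primary patient outcomes are selected analgesics’ side effects (constipation, nausea, emesis, and concentration difficulties), self-efficacy, and knowledge of cancer pain management". For caregivers: "Primary FC outcomes are self-efficacy and knowledge of cancer pain management". Pain comes below these: "The secondary outcomes are patients’ average and worst-pain intensity". That is six patient and two caregiver primary outcomes, with no order among them and no lead outcome.

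The Data analysis section gives one error level for everything: "An intent-to-treat analysis will be applied, using a significance level of .05".

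Constipation appears twice. The diary section lists it among the symptoms rated 0–10 and says "Our analysis will focus on constipation, nausea, emesis, and concentration difficulties". The CAS section describes an eight-item scale with a 0–16 total that "is completed weekly to measure the presence and severity of constipation", and Table 2 lists the CAS against constipation. Neither section says which measure is the primary outcome.

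For aim 1 the plan reads "Generalized linear mixed models will be applied to determine differences between the IG and the CG analgesic side effect developments throughout the intervention". It notes that each model yields group, time and group-by-time effects. Aim 2 has the same type of model for patient and caregiver knowledge. Under aim 3, caregiver self-efficacy enters only Pearson correlations. Patient self-efficacy has no stated analysis.

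**The concern.** A .05 level controls the error of one test. The conclusion that the programme reduces side effects rests on four outcomes, and the conclusion that it improves knowledge rests on two. With no lead outcome and no order, one nominally significant result among several could carry the whole efficacy statement, and the error attached to that statement would be well above 5%.

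Two choices also remain open until results are seen. One is which constipation instrument counts. The other is which of the effects from each mixed model decides the comparison. The trial is unblinded, so settling both in advance matters more than usual. The Discussion links efficacy to use of the programme in clinical practice, so a chance finding on one side effect would have consequences.

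**Working it through.** **Inputs from the document**
- Primary outcomes: 6 patient + 2 caregiver = 8 (section on quantitative variables and measurement).
- Outcomes with a described between-group model: 4 side effects (aim 1) + 2 knowledge scores (aim 2) = 6 (Data analysis).
- Constipation instruments: 2 (diary item and CAS).
- Level: .05. Sidedness is not stated; two-sided is assumed.
- Sample size: 136 evaluable patients, 35% attrition, 1:1 allocation, FCs expected for 50% of patients.

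**Assumption:** the document gives no correlation between outcomes. The range 0 to 0.5 is shown, equal for all pairs.

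**The plan's own figure.** 136 / (1 − 0.35) = 209.2, rounded up to 210. This reproduces, and gives 136 / 2 = 68 evaluable patients per arm. That size was derived for pain, which is secondary here.

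**Family-wise error.** This is the chance of at least one significant result when no true effect exists. For k independent tests it is 1 − 0.95^k. For correlated tests, the values come from equicorrelated two-sided z-tests each at .05.

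| Tests counted | k | Independent | Correlation 0.3 | Correlation 0.5 |
|---|---|---|---|---|
| Aim 2: patient and FC knowledge | 2 | 9.8% | 9.5% | about 9% |
| Aim 1: four side effects | 4 | 18.5% | 17% | 16% |
| Aim 1 with both constipation measures | 5 | 22.6% | 21% | 18% |
| All six described tests | 6 | 26.5% | 24% | 21% |
| Six, plus the second constipation measure | 7 | 30.2% | 27% | 23% |
| All eight named primaries | 8 | 33.7% | 30% | 25% |
| Eight, with both constipation measures | 9 | 37.0% | 33% | 27% |

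The last two rows require between-group tests of self-efficacy that the plan does not describe.

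**Price of Holm within each aim.** By normal approximation with 80% power, the detectable standardised difference is d = (z for 1 − α/2 + 0.842) × √(2/n), with n per arm.
- Aim 1, n = 68. At α = 0.05: (1.960 + 0.842) × √(2/68) = 0.48. At the first Holm step, α = 0.05/4 = 0.0125: (2.498 + 0.842) × √(2/68) = 0.57.
- Aim 2, FC knowledge. If attrition is also 35%, 210 × 0.50 × 0.65 = 68 caregivers, or about 34 per arm. At α = 0.05: 2.802 × √(2/34) = 0.68. At α = 0.05/2 = 0.025: (2.241 + 0.842) × √(2/34) = 0.75.

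**The case against.** A reader might infer that all eight outcomes are each tested at .05, so that the chance of a false efficacy claim is about one in three. The document does not support that. The two self-efficacy outcomes have no described group comparison, and 33.7% also needs independence. Ratings of four symptoms by the same patients, and knowledge within patient–caregiver pairs, are unlikely to be independent.

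A reader might also infer that the plan adopts a rule under which any one significant outcome establishes efficacy. No section says so; the error rates above are conditional on results being read that way.

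The strongest defence is that the aims are separate questions, the two knowledge tests concern different populations, and the adjustment method and deciding contrast are commonly left to an analysis plan, which is not shown here. Much of this stands. The absence of a named adjustment procedure in a condensed article is not in itself the fault, and the error should be judged by aim rather than over eight outcomes. What remains is that choosing the primary outcomes and the instrument for each is a protocol decision. This protocol makes it by naming eight unranked outcomes, one of them measured twice. Judged by aim, aim 1 alone is still at 16–19%.

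On constipation, the diary section's statement of focus, together with the CAS score's role in triggering a management plan, can be read as making the diary item the analysed measure. Because Table 2 lists the CAS against constipation as a study variable, the ambiguity is reduced but not removed.

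**Conclusion.** The concern holds as a fault in how the primary outcomes are fixed. There is no lead outcome, constipation has two candidate measures, and self-efficacy is labelled primary without a matching efficacy analysis.

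The size that matters is per aim: about 16–19% for the side-effect claim (up to 22.6% if both constipation measures are tested and independent) and about 9–10% for knowledge. Across the six described tests it is about 21–27%. Figures of 34–37% apply only if all eight outcomes, or nine measures, were tested independently.

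These figures rest on two-sided tests at .05, no true effects, an assumed correlation of 0 to 0.5, one test per outcome, and any single significant result being taken as efficacy. Accepting either the group or the group-by-time effect as success could raise them. An adjustment in an analysis plan not shown would lower the error, but the outcome set stated here would still need correcting. Severity: should-fix.

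**What to change.** In the outcomes section:
1. Name one constipation measure, diary item or CAS, as the primary one and call the other supportive.
2. Either name one primary outcome per aim and make the others secondary, or keep the present outcomes and apply Holm within each aim (four side effects; two knowledge outcomes).
3. Name one treatment contrast per outcome. The aim 1 text, which speaks of how side effects develop over the intervention, points to group-by-time.
4. Call self-efficacy secondary for patients and caregivers, unless a between-group test is added.

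Unadjusted confidence intervals can be reported alongside.

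Cost: about a paragraph of text, with no new patients, visits or data. Under Holm, the first-step detectable difference rises from about 0.48 to 0.57 for side effects, and from about 0.68 to 0.75 for caregiver knowledge if about 34 caregivers per arm remain. One primary outcome per aim avoids that loss of sensitivity, but requires the investigators to choose which side effect and which knowledge score carries each claim.
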